## Statistical Analysis

The data will be entered into Epidata version 3.1 and analyzed using STATA version 16 software. After cleaning and coding the data, sociodemographic characteristics and clinical information will be described by frequency, percentage, mean and standard error, or median and inter-quartile range based on normal distribution of the data.

**Content validity**: whether the questionnaire could be understood by the patients and expert, and whether all important and relevant items had been included by the expert panel will be evaluated. Face validity, the extent to which the questionnaire is a measure of what it is intended to measure in the opinion of patient and expertise will be evaluated by the expert committee through the adaptation process ([124](#_ENREF_124)). Experts will evaluate the comprehensiveness and the relevance using the scale that range from 1- 4 (1 = not relevant, 2 = somewhat relevant, 3 = quite relevant and 4 = highly relevant) ([125](#_ENREF_125), [126](#_ENREF_126)). Experts’ agreement on relevancy will be calculated using the Content Validity Index (CVI), and agreement ≥ 80% will be considered acceptable ([119](#_ENREF_119), [125](#_ENREF_125)). Moreover, the extent to which the tool is acceptable to participants will be evaluated using the estimated time required to fill out (respond to) the questionnaire, percentage of a fully completed tool, percentage of difficult items, and level of missing data ([127](#_ENREF_127)). The questionnaires’ content validity will be evaluated to ensure that there are only a few missing responses, used the full range of scores with little skew, have few ceiling (best possible score) or floor (poorest possible score). Floor and ceiling effects will be computed by percentage frequencies of the lowest and highest score achieved. Accordingly, ceiling and floor effects are considered presented if > 15% of participants achieved this score ([120](#_ENREF_120)). The presence of ceiling and floor indicates that the tool fails to measure extreme symptoms.

**Construct validity:** Construct validity will be evaluated by explanatory factor analysis using principal component analysis (PCA) and known-group validity. To run the factor analysis, its appropriateness will be determined by Kaiser-Meyer-Olkin (KMO) statistics and Bartlett’s test of sphericity. The value of Kaiser-Meyer-Olkin (KMO) is acceptable if it is > 0.5 ([128](#_ENREF_128)) and Bartlett’s test is acceptable if it is significant, P-value < 0.05 ([129](#_ENREF_129)). To identify the number of meaningful factors, the Scree plot representing eigenvalues associated with each factor will be used. Factors with eigenvalues > 1 will be considered meaningful and retained for rotation ([130](#_ENREF_130)). In addition, to estimate factor correlations, the varimax orthogonal rotation procedure will be used, and communalities and factor loadings ≥ 0.4 will be considered sufficient ([131](#_ENREF_131)). Items with factor loading ≥ 0.4 on more than one factor will be considered to be cross-loading ([128](#_ENREF_128)). To evaluate the known-group validity, the median difference of POP-SS values among the four stages of POP as classified by the POP-Q system will be compared by using the Kruskal-Wallis test.

**Criterion Validity:** How well the questionnaire correlates with an existing gold standard, will be evaluated by comparing the POP-SS score with the stages of prolapse confirmed through pelvic examination. Spearman’s correlation coefficient (SCC) and Kruskal-Wallis test will be used for statistical analysis. The size of the correlation coefficient will be interpreted as: 0.8 – 1.0 excellent, 0.6 - 0.8 very good, 0.41 – 0.6 good, 0.21-0.4 sufficient and 0.00-0.2 poor ([132](#_ENREF_132)).

**Reliability test:** Questionnaire reliability will be assessed using agreement and consistency indices. Cronbach alpha between 0.7 and 0.95 ([120](#_ENREF_120)) will be considered adequate for the internal consistency of the POP-SS questionnaire. Each item’s reliability will be analyzed by assessing its item-total correlation and the overall reliability if a specific item is deleted. Item-total correlation of ≥ 0.5 and inter-item correlation of ≥ 0.3 will be considered adequate ([133](#_ENREF_133)).

Test-retest reliability will be computed based on the Intra-class Correlation Coefficient (ICC). Single rating, absolute agreement, and a two-way mixed-effect model will be used and an Intra-class Correlation Coefficients (ICC) of ≥ 0.7 will be accepted ([120](#_ENREF_120)).

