## The Original POP-SS questionnaire

The original version of the POP-SS was initially developed by [name] in English Speaking women ([16](#_ENREF_16)). Later it was translated to and validated in Turkish, Amharic, and Chinese ([113-115](#_ENREF_113)). The POP-SS has seven questions with a five-point Likert scale which ranges from zero to four (0= never felt symptom, 1= occasionally, 2= sometimes, 3= most of the time, and 4= all of the time), a higher score indicating severe symptoms ([16](#_ENREF_16)). The participants will be asked how often they have had the following symptoms in the last four weeks: 1) A feeling of something coming down from the vagina? 2) Uncomfortable feeling in the vagina that worsens when standing? 3) A heaviness feeling in the lower abdomen? 4) A dragging feeling in the lower back? 5) A difficulty of emptying the bladder? 6) A feeling of incomplete bladder emptying? 7) A feeling of incomplete bowel emptying? The total score will be calculated by summing up all responses for the seven-question and the total score will range from 0 to 28. If the participants' total response score is different from zero, she will be considered as having symptoms of prolapse.

To increase the accuracy of measurements, instrument (data collection tool) translation, cross-cultural adaptation, and validation for the language of the target population are mandatory ([116-118](#_ENREF_116)). Therefore, this study is aimed to translate and validate the POP-SS tool in Sidamu Afoo.

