## Sample Size

To ensure the statistical robustness of the analysis, the sample size is determined based on the recommendation of at least 5-10 subjects per item of the tool by the consensus-based Standards for the Selection of the Health Measurement Instruments (COSMIN) ([120](#_ENREF_120), [121](#_ENREF_121)). Accordingly, the estimated sample size is 70 (10 subjects per item).

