## Data Measurements

At each visit, women's adherence to pelvic floor muscle training will be evaluated by their pelvic muscle trainer. At week two, women will be assessed for adherence to pelvic floor muscle exercise in the last two weeks (three times a day, once a day, a more than once per week, once per week, a more than one days per week). At weeks six, 10, and 15, they will be assessed for adherence to pelvic floor muscle exercise in the last four weeks using similar questions used on week two (three times a day, once a day, a more than once per week, once per week, a more than one day per week). In addition, they will be assessed for prolapse symptoms at weeks 10 and 15.

At the end of six months, the overall adherence to training protocol will be evaluated from their dairy or report of pelvic muscle trainer. Women’s adherence to training protocol is considered adequate when they complete at least 80% of the training sessions (24). This will be calculated at each visit based on the training session and finally compiled.

The primary outcome of the study is a change in prolapse symptoms measured by POP-SS. The POP-SS is the same measurement with study one which measures the frequency of prolapse symptoms in the last four weeks, measured by seven items with a Likert-scale of 0 to 4 scale (0= never felt symptom, 1= occasionally, 2= sometimes, 3= most of the time and 4= all of the time). The total score will be calculated by summing up all responses for the seven-question and the total score will range from 0 to 28, the highest value indicating the severity of prolapse symptoms (25, 26). At the end of the six months, the mean change in prolapse symptoms from the initial visit will be compared between the two groups (intervention and control groups) to measure the effect of pelvic muscle training.

The secondary outcome, women’s perceived change in prolapse symptom since the start of the intervention, will be measured as improved, the same, or worsened based on Patient Global Impression of Change (PGIC) (14, 27).

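### With 70 women and seven items, keeping every factor with an eigenvalue above 1 can make a one-factor POP-SS look multidimensional; parallel analysis should decide instead

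*Protocol*

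**What the plan says.** The protocol's Paper-I validates the Sidaamu Afoo version of the POP-SS. On the tool: "The POP-SS has seven questions with a five-point Likert scale" (The Original POP-SS questionnaire). The sample size is 70, from a recommendation of "at least 5-10 subjects per item of the tool" (Sample Size).

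Under Statistical Analysis, construct validity rests on a factor analysis by principal components and on a known-group comparison across prolapse stages. KMO above 0.5 and a significant Bartlett test decide whether the factor analysis is appropriate. A scree plot is named for finding the number of factors, without a numeric rule. The numeric rule is that "Factors with eigenvalues > 1 will be considered meaningful and retained for rotation". Varimax rotation follows, and loadings of 0.4 or more count as sufficient.

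Under reliability, Cronbach's alpha of 0.7 to 0.95 is adequate, and "Item-total correlation of ≥ 0.5 and inter-item correlation of ≥ 0.3 will be considered adequate".

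In Paper-III, Data Measurements, the trial's primary outcome is the summed score: "the total score will range from 0 to 28, the highest value indicating the severity of prolapse symptoms".

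**The concern.** The cut at 1 is the mean eigenvalue of a correlation matrix. It makes no allowance for chance. In a sample of 70 on seven items, the second eigenvalue of a scale with only one factor can exceed 1 through sampling error alone, and the plan would then call that factor meaningful and rotate it. The other steps do not correct this. KMO and Bartlett only ask whether there is enough correlation to analyse, and rotation spreads the items over whatever number of factors has been kept.

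At stake is the dimensionality result of Paper I. The validated tool is then used in Paper II and supplies the trial's primary outcome as a single sum. A false multi-factor report would sit beside that sum, and the protocol does not say how the two should be read together.

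**Working it through.** **The plan's own figure.** 10 women per item × 7 items = 70. It reproduces exactly.

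**What the adequacy limits imply.** For seven items with equal inter-item correlation r:
- alpha = 7r / (1 + 6r). At r = 0.25: 1.75 / 2.5 = 0.70. At r = 0.30: 2.1 / 2.8 = 0.75. At r = 0.73: 5.11 / 5.38 = 0.95. The alpha band therefore covers r of about 0.25 to 0.73.
- correlation of an item with the sum of the other six = 6r / √(6 + 30r). At r = 0.335: 2.01 / √16.05 = 0.50. At r = 0.30: 1.8 / √15 = 0.46.

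**Simulation.** Samples of n = 70 on seven items were drawn from a strictly one-factor model, with 3,000 to 10,000 samples per setting in most runs. Eigenvalues came from the Pearson correlation matrix, and a sample counted as a false positive if the second eigenvalue exceeded 1. Correlation and item distribution are assumptions, because the protocol gives neither. Ranges cover repeat runs, including more than one right-skewed item setting.

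| Latent r (equal loadings) | Continuous | Symmetric 5-point | Right-skewed 5-point |
|---|---|---|---|
| 0.30 | 53–54% | 67–68% | 87–92% |
| 0.35 | 27–29% | 42–43% | 72–79% |
| 0.40 | 11% | 21–22% | 52–62% |
| 0.45 | 3% | 8% | 30% |
| 0.50 | 1% or less | 2% | 14–24% |

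**Observed scale.** With 5-point items the observed r is below the latent r: latent 0.40 becomes about 0.37 (symmetric) or 0.33 (skewed), and latent 0.30 becomes about 0.275 or 0.24. Matched on an observed mean r of about 0.30, the false rate is 54% (continuous), 53% (symmetric) and 58–67% (skewed). At about 0.33 it is 38%, 37% and 52%.

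**Uneven loadings raise the rate.** Loadings of 0.8, 0.8, 0.7, 0.6, 0.5, 0.5 and 0.4 (mean r 0.37) gave 42% with continuous and 75% with skewed items.

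**Other steps of the plan.** At least 98% of these samples pass the KMO and Bartlett conditions, and the false rate is essentially unchanged. After varimax with the 0.4 loading cut, about 99% of the samples with a false extra factor had at least two factors each carrying two or more items, so the artefact looks like a clean structure.

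**Parallel analysis.** The 95th percentile of the second eigenvalue in random data (n = 70, seven items) is about 1.39, against the plan's 1. Judged this way, a false second factor appeared in at most 2.5% of samples in the equal-correlation settings examined (latent r 0.25 to 0.50).

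**The price.** With two true factors (items split four and three, r = 0.6 within and 0.3 between), parallel analysis found the second in about 55% of samples, against 98% for the cut of 1.

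**The case against.** Four points can be made for the plan.

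1. *The high rates belong to weak scales.* This largely stands. With equal loadings the rate falls below 50% once the observed mean r passes about 0.31 to 0.33. The top of the range (87–92%) occurs where skewed items have an observed r of about 0.24, under the plan's own 0.3 floor. Among samples with alpha of 0.70 to 0.95 and mean r of at least 0.3, the rates are 28% / 33% / 50% (continuous / symmetric / skewed) at latent r 0.30, and 8% / 15% / 35% at 0.40. If every item must also correlate 0.5 or more with the sum of the others, the rate drops to about 0–5%. However, few samples meet that when r is low, an uncorrected item-total correlation is a weaker test, and the protocol does not make the reliability limits a condition for the factor analysis.

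2. *The scree plot is also used.* True, but it has no stated rule, while the cut of 1 does.

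3. *A second factor could be real.* This stands. The items cover vaginal, abdominal and back, bladder and bowel symptoms, two of them on bladder emptying, and the protocol never claims one dimension. It limits what parallel analysis can prove, but it does not make the cut of 1 informative, since that cut often shows two factors whether or not two exist.

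4. *The trial does not depend on the result.* This stands. A reader might infer that a second factor would lead the validation to reject the 0 to 28 score. The documents do not support that: the sum is set without condition in Paper-I, in Paper II and in Paper-III, and nothing links the number of factors to dropping, splitting or rescoring it.

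**Conclusion.** The point holds as a risk of misreported dimensionality in Paper I. At n = 70 with seven items, the eigenvalue rule gives a false second factor in roughly 10% to 90% of samples from a one-factor scale at latent r of 0.3 to 0.4. At r of 0.5 the rate is about 2% or less with continuous or symmetric items, and about 14% to 24% with skewed items. These figures rest on assumed equal loadings and assumed item distributions; uneven loadings push them up.

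A reader might also infer that most samples would mislead whatever the data look like. That is not supported: it is true only near the plan's correlation floor, or with skewed items or uneven loadings. The trial's primary outcome is not changed by this.

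**What to change.** In Paper-I, Statistical Analysis, replace the eigenvalue cut as the test of whether a factor is meaningful. Suggested wording: *a factor is retained if its eigenvalue exceeds the 95th percentile of the corresponding eigenvalue from random data with the achieved number of women and seven items (parallel analysis); all eigenvalues and the scree plot are reported alongside.* For n = 70 the second eigenvalue then has to exceed about 1.39.

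Add that a one-factor result will be described as no second factor shown, and not as proof that the scale is unidimensional.

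The cost is a sentence or two and a short simulation, with no extra data. The price is sensitivity: a real, moderately correlated second factor may be missed at n = 70, as in about 45% of samples in the two-factor example (100 − 55), and more often if only two items, such as the bladder items, carry it.

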# **PAPER II**

Prevalence and risk factors of Pelvic Organ Prolapse among women in Sidama Region, Ethiopia; 2022**.**

## Specific Objectives

1. To determine the prevalence of Pelvic Organ Prolapse among women in Sidama National Regional State, Ethiopia
2. To identify risk factors associated with Pelvic Organ Prolapse among women in Sidama National Regional State, Ethiopia

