## Study Setting and Period

This study will be conducted in the Dale and Wonsho districts of Sidama National Regional State, Ethiopia from 01 June – 24 July 2022. Both woredas are known for their highly dense population and coffee production. Dale district (woreda) has 10 health centers and 33 health posts. Hamlin Fistula Center, which provides care for fistula cases and pelvic organ prolapse is found in Yirga-Alem town in Dale district. Wonsho district has five health centers and 17 health posts. According to the 2021 report of Sidama Regional Health Bureau, the total population of Dale district is 254,653 and that of Wonsho district is 129,730 ([134](#_ENREF_134)). According to the Ethiopian Central Statistical Agency, the female population accounts for 49.7% of Dale woreda population and 49.2% of Wonsho population ([135](#_ENREF_135)). Dale district has 36 rural and two urban kebeles while Wonsho district has 17 rural and one urban kebeles (smallest administrative units in Ethiopia).

In 2017, Hawassa University has established its own Health and Demographic Surveillance System site in Dale and Wonsho districts of Sidama Region. The HDSS site include 10 rural kebeles and two urban kebeles. The Surveillance site is called Dale-Wonsho Health and Demographic Surveillance Site (D-W HDSS). The Map of the HDSS site is obtained from previous study (Figure 2).

[figure not shown]

Figure 2: Map of Hawassa University Health and Demographic Surveillance System Sites from Dale and Wonsho Districts ([136](#_ENREF_136)).

.

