## Study Design

A community-based cross-sectional survey design will be used to determine the prevalence of pelvic organ prolapse among women in the Sidama region. In a survey study, data are collected either from the whole population or a subset of the population to answer the research question. These studies are useful to assess the burden of disease and inform the planning and allocation of resources. A survey study should be representative of the population to have valid generalization ([137](#_ENREF_137)).

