## Study Population

All women who have given birth (at least once) or ≥ 18 years old, and permanent residents (≥ 6months) of the Health and Demographic Survey Site of Hawassa University will be included in this study.

**Inclusion Criteria:** Women whose household information is found in the Health and Demographic Survey of Hawassa University and who have given birth or ≥ 18 years old will be included.

**Exclusion criteria:** Women who are pregnant (confirmed or suspected), in the postpartum period (six weeks), never practiced sexual intercourse, or severely sick during the data collection period will be excluded.

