## Sampling Techniques

A complex sample survey will be used to recruit study participants. A survey sampling is a process of selecting representative samples from the population and measuring the selected samples to get evidence about population parameters ([138](#_ENREF_138)). If the selection of study participants passes through a series of stages like multilevel sampling, cluster sampling, or stratification, it is called complex sampling. The features of large survey sampling are stratification, clustering, and unequal probability sampling ([138-141](#_ENREF_138)).

The current planned study will be conducted in the Dale and Wonsho districts of the Sidama region. The two districts were selected due to the accessibility of the sampling frame from the Health and Demographic Surveillance System (DHSS) of Hawassa University. The DHSS involved a total of seven rural kebeles (Wayicho, Hida Kality, Shoye, Dagiya, Magara, Danshe sire and Gidamo); and one urban kebeles (Aposto) from Dale district, and three rural kebeles (Mamana, Bokaso and Gishire); and one urban kebele (Wonsho 01) from the Wonsho district. The list of households from these kebeles will be used for the sampling frame in the current planned study.

In this study, Hawassa University Health and Demographic Surveillance System (HDSS) site will be initially stratified into two districts (Dale and Wonsho). Then each district will be re-stratified into urban and rural kebeles. Since there are only one urban kebeles included in to the DHSS from each district, both kebeles will be selected to ensure representativeness. From rural kebeles, representative kebeles will be selected from both districts (four rural kebeles from Dale and two rural kebeles from Wonsho district) based on their selection probability. If the selected rural kebeles (clusters) are adjacent to each other, the second cluster will be replaced by the next kebele (cluster) to create a buffer zone. Finally, equal number, 101.6 approximated to 102, eligible women from each kebele (clusters) will be selected using computer-generated random numbers. This approximation will adjust the sample size to 816 to sample equal number of participants from each clusters. Therefore, this study includes four strata: Dale-Rural, Dale-Urban, Wonsho-Rural, and Wonsho-Urban; eight clusters (kebeles) and 816 eligible women (Figure 3). If there is more than one eligible woman in the selected household, one of them will be selected by the lottery method.

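### Paper II claims prevalence and risk factors for women of Sidama Region, but its design can estimate them only for residents of the Dale-Wonsho surveillance kebeles

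*Protocol*

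**What the plan says.** **The claim.** Paper II, Specific Objectives, sets out "To determine the prevalence of Pelvic Organ Prolapse among women in Sidama National Regional State, Ethiopia", and the second objective does the same for risk factors. The Paper II title and Study Design also name the region. Significance of the Study says the work will determine prevalence and risk factors for women of the regional state and that the regional health bureau will use the findings. Expected Outcome promises prevalence and risk factors for the community of the Sidama region.

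**The population that can be sampled.** Study Population admits only "permanent residents (≥ 6months) of the Health and Demographic Survey Site of Hawassa University will be included in this study".

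**How the area was chosen.** Sampling Techniques states: "The two districts were selected due to the accessibility of the sampling frame from the Health and Demographic Surveillance System".

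**How large the frame is.** Study Setting and Period gives "Dale district has 36 rural and two urban kebeles while Wonsho district has 17 rural and one urban kebeles", and for the surveillance site "The HDSS site include 10 rural kebeles and two urban kebeles". Sampling Techniques then takes 4 of 7 rural kebeles in Dale, 2 of 3 in Wonsho, and the single urban kebele of each district.

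**How the data are weighted.** Data Management and Analysis weights by selection probability and adjusts for non-response with auxiliary data from the surveillance system.

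**The protocol's own test.** Study Design states: "A survey study should be representative of the population to have valid generalization".

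**The concern.** The population named in the objectives differs from the population that can enter the sample. Districts were not drawn from the region, and the kebeles in the frame are those the surveillance site happens to contain. Nothing in the plan connects the estimate to women outside the site.

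At stake is what the survey may conclude. A regional prevalence figure would go to a regional health authority for planning, and its interval would reflect only sampling within the surveillance kebeles. Readers would take that interval as the uncertainty about the region, which it is not.

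**Working it through.** **1. Coverage of the frame** (counts from Study Setting and Period and Sampling Techniques)

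- Kebeles in the two districts: 36 + 2 + 17 + 1 = 56.
- In the surveillance frame: 10 + 2 = 12, and 12/56 = 21%. Surveyed: 4 + 2 + 1 + 1 = 8, and 8/56 = 14%.
- Rural: 10 of 53 are in the frame (19%). Urban: 2 of 3 (67%).
- Urban share by count: 2/12 = 17% of the frame against 3/56 = 5% of the districts. Kebele populations are not given, so this compares counts only.

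The frame is therefore not shown to represent even its own two districts. Dale also contains a centre that provides prolapse care. The documents do not say whether that moves prevalence up or down.

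**2. The planned precision**

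Inputs from Sample Size Determination: p = 0.563, 95% confidence, design effect 2, non-response 7%. The margin d is not stated.

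- n0 = z²p(1−p)/d². With d = 0.05 this is 378.05.
- 378.05 × 2 = 756.09, and 756.09/0.93 = 813.0, which matches the stated 813. A margin of 0.04 gives 1,270 and 0.06 gives 565, so d = 0.05 is inferred.

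The plan thus aims at about ±5 points for the population that is sampled. The calculation contains no term for districts, nor for kebeles outside the site.

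**3. What a shift does to a ±5-point interval read as regional** (the shifts are assumptions; the documents give no value)

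The standard error is 5/1.96 = 2.55 points. If the site differs from the region by b, coverage is Φ(1.96 − b/2.55) − Φ(−1.96 − b/2.55).

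- b = 2.5 points: Φ(0.98) − Φ(−2.94) = about 83%.
- b = 5 points: Φ(0) − Φ(−3.92) = about 50%.
- b = 10 points: Φ(−1.96) − Φ(−5.88) = about 2.5%.

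Enlarging the sample makes this worse, because the interval narrows around the shifted value.

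**4. Interval for the surveillance population, with and without a finite-population correction**

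Assumptions: equal kebele sizes, so stratum weights W are 7/12, 3/12, 1/12 and 1/12; m = 102 × 0.93 = 94.9 women examined per kebele; design effect 2, so ICC = 1/(94.9 − 1) = 0.0107; multiplier 1.96.

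Variance = ΣW²[(1−f)τ²/a + σ²/(a·m)], where a is kebeles taken, f is the first-stage fraction, τ² = ICC × 0.2460 = 0.00262 and σ² = 0.2434.

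- ΣW²/a = 0.0851 + 0.0313 + 0.0069 + 0.0069 = 0.1302. With (1−f) = 3/7, 1/3, 0, 0 it becomes 0.0469.
- Within-kebele part: 0.1302 × 0.2434/94.9 = 0.000334.
- Between-kebele part: 0.1302 × 0.00262 = 0.000341 without the correction, 0.0469 × 0.00262 = 0.000123 with it.
- Half-width: 1.96√0.000675 = 5.1 points without, 1.96√0.000457 = 4.2 points with, or 18% narrower. With 4 degrees of freedom (6 rural kebeles less 2 strata) the figures are 7.2 and 5.9.
- If the fractions are entered at the first stage and no second stage is declared, the within-kebele part shrinks too: 0.0469 × (0.00262 + 0.2434/94.9) = 0.000243, a half-width of 3.06 points. That is 27% below 4.19, and both urban strata contribute no variance at all.

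**The case against.** **The limits are visible.** The Summary names eight kebeles in two districts, Study Population restricts eligibility, and Sampling Techniques gives the reason for the choice. Prevalence is also not an outcome of the trial in Papers III and IV. This is fair and keeps the point modest. But the objectives and the intended use still name the region, and stating the setting elsewhere does not correct them.

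**A reader might infer that the interval is also too wide for the population actually sampled**, given first-stage fractions of 4/7, 2/3, 1 and 1. The documents do not support that. No section says a finite-population correction is omitted. Data Management and Analysis calls for estimation that accounts for the complex design, and the survey set-up is ordinary content of a statistical analysis plan.

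**A reader might also enlarge the effect by borrowing the trial's ICC of 0.03**, which gives 7.0 against 5.1 points. That ICC belongs to a different outcome. At 94.9 women per kebele it implies a design effect of 1 + 93.9 × 0.03 = 3.8, against the 2 planned for the survey.

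**Calling the interval too narrow for the region** is right in direction if districts differ at all. But the protocol gives no regional interval and no between-district variance. Because the districts were not drawn at random, adding such a variance would not produce a valid regional interval. Width is the lesser issue.

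**Conclusion.** The mismatch between target and frame stands on the protocol's own text and fails the protocol's own test for generalization. The survey can estimate prevalence and associations for women of the Dale-Wonsho surveillance kebeles, which are 12 of 56 kebeles in two districts chosen for access. It supports no design-based estimate or interval for Sidama Region.

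The size of any regional bias is unknown. The coverage figures of 83%, 50% and 2.5% rest on assumed shifts of 2.5, 5 and 10 points and only show how sensitive a regional reading would be.

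It would go too far to conclude that the error bars are wrong for the surveillance population. The change from 5.1 to 4.2 points is what a properly specified correction would do under equal kebele sizes and the planned design effect. It is not evidence of an error in the plan.

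**What to change.** Restate the Paper II target population in the title, objectives and conclusions as women of the Dale-Wonsho surveillance kebeles. Carry the same wording into Study Design, Significance of the Study and Expected Outcome. Label any statement about Sidama Region as an extrapolation and give the reasons a reader should accept or doubt it. The cost is wording, and the headline claim becomes narrower. If the regional claim is to stay, districts would have to be sampled at random across the region, which is a different and much larger survey.

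If a finite-population correction is used for the surveillance population, three things go with it:

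- a declared second stage (women within kebeles);
- certainty treatment of the two one-kebele urban strata;
- inclusion probabilities that reflect both the selection rule and the replacement of adjacent rural kebeles in Sampling Techniques, because 4/7 and 2/3 are not then simple random fractions.
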